#### Changes in Medicine

Information on medicine for both groups will be collected at enrollment and every week from the electronic patient record during a 6-month period. Changes in medicine over time will be analyzed.

#### Pain Assessment

In line with the recommendations for supplementing the EORTC QLQ-C15-PAL with focused measures, if more information on a specific content area is warranted [29], and in accordance with the Expert Working Group of the European Association for Palliative Care [30], we incorporated the Brief Pain Inventory Short Form, a pain measurement tool [31]. The Brief Pain Inventory rapidly assesses the severity of pain and its impact on the patient’s functioning. In this study, we incorporated the 11-point numeric rating scale (0-10) for pain intensity as well as 7 items focusing on the impact of pain on functioning in relation to activity, mood, ability to walk, work, relation to other people, sleep, and general joy of life rated on an 11-point numeric rating scale (0=no impact to 10=full impact). The internal consistency of the Brief Pain Inventory (Cronbach α) ranges from .77 to .91, and more specifically, for the pain intensity scale, Cronbach α ranges from .78 to .96 [32].

#### Sense of Security

To evaluate the patient’s sense of security using the TelePal platform, we developed a single item (“Overall, how would you rate your sense of security over the past 24 hours?”), rated on a 5-point scale (1=very unsafe to 5=very safe), to be used in this study.

#### Use of TelePal Platform and Experiences Using the TelePal Platform

Qualitative exploration of the patients’, their relatives’, and the HCPs’ experiences using the TelePal platform will be collected during semistructured interviews inspired by Brinkmann and Kvale [33]. Patients will be selected randomly to participate in interviews. Interviews with patients and relatives will be conducted after 4, 8, and 12 weeks. Interviews with HCPs will be conducted after 6 and 12 months. All interviews with patients, relatives, and HCPs will be conducted until data saturation has been reached. To analyze which parts of the TelePal platform are being used and for how long, time log files for log-in and log-out of patients, relatives, and HCPs will be analyzed at the end of the project. Consent for the extraction of log files from the database will be received from patients, relatives, and HCPs.

#### Evaluation of Cost of Health Care Services

The data used to determine QALYs will come from the EQ Visual Analog Scale of the EQ-5D questionnaire [26] (see description in the Quality of Life section). Patients will be asked to answer the EQ-5D health questionnaire twice, first in week 1 of the study and then in week 4, in order to determine QALYs [26]. The questionnaire will be completed by the intervention group on TelePal, and the control group will complete the questionnaire on TelePal or on paper. Furthermore, a cost-effectiveness analysis will be conducted by calculating the differences in clinical efficacy and differences in average cost per patient [34,35]. The cost parameters are numbers of phone or video calls from the palliative team, equipment used, driving distance, personal use in palliative care, visits from GPs, outpatient clinic visits, numbers of hospitalizations, readmissions, length of stay, and visits from the palliative team.

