## Introduction

The World Health Organization defines end-of-life palliative care as “prevention and relief of suffering, by means of early identification and impeccable assessment and treatment of pain and other problems, physical, psychosocial and spiritual” [1]. The aim of palliative care is to provide relief from pain and other distressing symptoms offered by health care professionals (HCPs) at a general or specialist level, with a focus on addressing the needs of patients and their families [1,2]. More than 20 million people worldwide are estimated to be in need of end-of-life palliative care, equivalent to 377 adults in a population of 100,000, the majority of these being adults aged 60 years and older [2].

In Denmark, as in most other Western European countries, palliative care is provided at 2 different levels, a general and a specialist. The general level comprises HCPs, such as general practitioners (GPs) and primary care nurses, who do not perform palliative care on a full-time basis. The specialist level comprises specialized palliative care (SPC), where HCPs perform palliative care on a full-time basis at a specialist level [3]. It is expected that the basic level palliative care can address around 70%-80% of the patients in need of palliative care. The remaining 20%-30% of patients, having more complex problems, need SPC. SPC consists of specialized palliative care teams (SPCTs) placed at large hospitals serving a wider geographical area with home visits and cross-sector communication with patients, relatives, and other HCPs capable of caring for the patients.

Among patients receiving SPC, more than 90% are diagnosed with cancer [4], with the remaining cases divided among patients diagnosed with terminal cardiac insufficiency, terminal chronic obstructive pulmonary disease, and terminal neurological disorders [2,4].

There are several challenges associated with SPC, such as the very short time span from referral to the end of the patient’s life [4] and the fact that patients are very ill and may therefore find it hard to travel to an outpatient clinic and that SPC unit often has a relatively small staff [2,5-7]. The need for SPC is expected to rise in the future, as the number of patients dying from life-threatening diseases, including cancer, is increasing [5,8]. As an increasing number of these patients prefer to be cared for at home, the demand for SPC is expected to increase [5,8].

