### Ethical Considerations

This study was approved by the ethical committee in Northern Jutland (N-202000094) and registered at ClinicalTrials.gov (NCT04995848). This study will be conducted according to the Declaration of Helsinki. Patients in palliative care and their relatives are a vulnerable group and will be informed thoroughly about the purpose of the study. Accordingly, it is specified that the patient can withdraw their consent at any given time in the study without having any consequences for their treatment. Individuals will be considered as participants in the trial, whereas their relatives will not be considered as participants. However, they are invited to voluntarily participate in the use of the digital platform TelePal. To clarify and ensure that all relatives are fully informed about the study and feel safe about their participation, a written letter of information was sent to all relatives. Patients are enrolled in the study for a maximum of 6 months or until (1) they stop being followed by the palliative team due to lack of symptoms or (2) they are diagnosed with delirium based upon the Confusion Assessment Method score [22,23]. Patients who develop cognitive impairment will be dismissed from the study, and patients who develop delirium will also be dismissed, and data collection will end immediately.

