**Secondary**				
	Changes in medicine	Weekly for 6 months	✓	✓
	Pain assessment	Weekly	✓	✓
	Feeling of security	Twice a week	✓	✓
	Patients’ experiences	Interviews will be conducted after 4 weeks	✓	
	Relatives’ experiences	Interviews will be conducted after 4 weeks and after 3 months	✓	
	Health care professionals’ experiences	Interviews will be conducted at 6 and 12 months		
	Use of the TelePal platform and telepalliation program	Analysis at the end of the project	✓	✓
	Cost of health care services	Week 1 and week 4, and analysis at the end of the project	✓	✓
	Quality of life associated with cost of health care services	Week 1 and week 4, and analysis at the end of the project	✓	✓

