#### Quality of Life

The EORTC QLQ-C15-PAL (European Organisation for Research and Treatment of Cancer Quality of Life Questionnaire Core 15 Palliative Care) [24] questionnaire will be used to measure QoL as the primary outcome. The EORTC QLQ-C15-PAL was developed by the European Organization for Research and Treatment of Cancer to measure the QoL for patients in palliative care. It is a briefer version of the EORTC QLQ-C30-PAL I, as this patient group is often not able to complete extensive self-report measures. It consists of 15 items, of which, all but one (global QoL) is self-rated on a 4-point Likert scale (1=not at all to 4=very much), whereas global QoL is rated on a 7-point Likert scale (1=very poor to 7=excellent). In this study, we did not use the global QoL item. Items are used to calculate scores on 2 multi-item functional scales (emotional and physical), 2 multi-item symptom scales (fatigue and pain), and finally, they contribute to 5 single-item symptom scales (nausea or vomiting, lack of appetite, shortness of breath, constipation, and sleeping difficulties). The EORTC QLQ-C15-PAL is considered to have good content validity [24], and a recent study comparing measures of QoL in palliative care found acceptable internal consistency and test-retest reliability as well as sensitivity of the EORTC QLQ-C15-PAL, while overall results indicated that no other QoL measure is superior to use in this patient group [25].

In addition, the EQ-5D health questionnaire was used to determine QALY to support our analysis on the cost of health care services, as no other QoL measure is validated for this purpose. Hence, we incorporated EQ-5D, the EQ Visual Analog Scale from the EQ-5D, which records the patient’s self-rated health on a vertical visual analog scale using the end points, the best health you can imagine and the worst health you can imagine. This scale can be used as a quantitative measure of health outcomes that reflect the patient’s own judgment [26]. Studies have shown good construct validity and responsiveness in palliative care [27], and a recent systematic review finds that the EQ-5D has excellent psychometric properties across a broad range of populations [28].

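### The QALYs are to come from the EQ Visual Analog Scale, which has no value for death and is not a preference-based utility, so the results would not be QALYs

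*Protocol article*

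**What the plan says.** The protocol article, under Evaluation of Cost of Health Care Services, names the source of the QALY data: "The data used to determine QALYs will come from the EQ Visual Analog Scale of the EQ-5D questionnaire". The same section fixes the timing: the questionnaire is answered twice, "first in week 1 of the study and then in week 4, in order to determine QALYs".

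Under Quality of Life, the article gives the reason for including the instrument: "the EQ-5D health questionnaire was used to determine QALY to support our analysis on the cost of health care services". It adds that it regards no other quality-of-life measure as validated for that use. It then describes the VAS as a self-rating on a vertical line "using the end points, the best health you can imagine and the worst health you can imagine". No conversion to an index and no value set is mentioned.

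Table 1 has one row for the cost of health care services and one for the quality of life linked to that cost. Both carry the same schedule: "Week 1 and week 4, and analysis at the end of the project". Under Ethical Considerations, "Patients are enrolled in the study for a maximum of 6 months". The Introduction stresses "the very short time span from referral to the end of the patient’s life". Adverse Events and Dropouts says that deaths are recorded. Statistical Analysis says that, where data are missing, the questionnaires received will be analysed.

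**The concern.** A QALY multiplies time by a weight on which dead is 0 and full health is 1, and the weight should express a preference between health states. The EQ-5D supplies such a weight through its five-dimension profile and a value set. The VAS that accompanies it asks patients how good their health is, between two imagined extremes. It does not locate death and elicits no trade-off. The article justifies the EQ-5D as the instrument suited to QALYs, then takes the QALY data from the part of it that does not provide them.

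This is a choice that the article states, not a detail it leaves open. The cost of care is a listed secondary outcome, and the Discussion looks forward to showing that the programme is cost-effective. A figure labelled QALY but built from VAS scores could not be compared with QALY results from elsewhere. In a population where death is common and early, a scale without a value for death is a particular weakness.

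**Working it through.** The article states no QALY figure, so there is none to reproduce. The checks concern the scale, the window, early deaths and the cost period.

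**1. Scale.** Let v be a VAS reading rescaled to 0–1 (worst to best imaginable health), and let d be the unknown position of dead on that line. A weight with dead at 0 would be (v − d)/(1 − d), and a difference between arms would be multiplied by 1/(1 − d). The plan does not ask for d, so the VAS cannot be placed on the dead-to-full-health scale. Even with d known, v would still be a rating and not a preference.

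**2. Window.** Inputs: readings in weeks 1 and 4 (Evaluation of Cost of Health Care Services; Table 1); maximum enrolment 6 months, about 26 weeks (Ethical Considerations).
- Span: 4 − 1 = 3 weeks = 3/52 = 0.058 year. With a weight of 1 throughout, this is the most QALY that a patient can accrue.
- Share of the maximum enrolment: 3/26 = 11.5%. Six months is a maximum, so the share is larger for a patient followed for less time.
- Illustration: assume no difference between arms at week 1 and 0.10 at week 4 on a 0–1 scale. The area under the curve is 0.5 × 0.10 × 3/52 = 0.0029 QALY, or 0.5 × 0.10 × 21 = 1.05 days.

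**3. Deaths before week 4.** The article gives no mortality rate. Assume exponential survival from week 1 with median m weeks and a constant weight while alive.
- Proportion dead by week 4: 1 − 0.5^(3/m).
- Mean time alive in the window: (1 − 0.5^(3/m)) × m/ln 2.
- Overstatement if only patients with both readings were averaged, compared with scoring 0 after death: 3 ÷ (mean time alive) − 1. The constant weight cancels.

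| Assumed median (weeks) | Dead by week 4 | Of 91 per arm | Mean weeks alive in window | Overstatement |
|---|---|---|---|---|
| 4 | 41% | 36.9 | 2.34 | 28% |
| 8 | 23% | 20.8 | 2.64 | 14% |
| 13 | 15% | 13.5 | 2.77 | 8% |
| 26 | 8% | 7.0 | 2.88 | 4% |

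The last column shows what a completers-only average would do. The article does not say that this average will be used.

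**4. Cost period.** Three places bear on it. Table 1 gives costs the same week 1 and week 4 schedule as the QALY measure. The cost section lists hospitalizations, readmissions, length of stay, visits and other items per patient without a period. Enrolment runs for up to 6 months. Together they do not settle whether costs cover weeks 1–4 or the whole of a patient's participation.

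**The case against.** The strongest reply is that only the choice of the VAS is stated outright, and that more can easily be read into the text than it holds. Three stronger readings are tempting.

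- **That the plan excludes the dead.** No passage says so. Deaths are recorded, so a value of 0 could be assigned from the date of death. How deaths enter a QALY is also something that an article may leave to a fuller plan. What stands is narrower: the named scale has no value for death, and a patient who dies before week 4 has no second reading.
- **That 3 weeks of QALYs are set against 6 months of costs, inflating the ratio many times over.** No passage sets a 6-month cost window, and Table 1 points to weeks 1 and 4 for both. A multiple of that kind would also need every patient to live to week 26, against what the Introduction says about survival. What stands is that the cost period needs stating.
- **That a cost-per-QALY ratio is defined and its denominator is wrong.** The cost-effectiveness analysis is described in terms of clinical efficacy and average cost, and no incremental cost per QALY is defined. The Quality of Life section does tie QALYs to the cost analysis, so the link is plausible but not fixed.

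The objection that this is only a secondary economic outcome is also fair. It limits the importance of the point but does not answer it.

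**Conclusion.** The plan is wrong as written on the source of the QALY weight. This rests on the article's own words in two sections and needs no assumption about data. Figures computed from the VAS would not be QALYs and could not support a cost-per-QALY statement.

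Two further points are matters of limits and clarity. The two readings span 3 weeks and can hold at most about 0.058 QALY per patient, and the cost period must be stated so that both sides cover the same time. The 8% to 41% dead by week 4, and the 4% to 28% overstatement in a completers-only average, hold only under the assumed medians of 26 down to 4 weeks and exponential survival. They show why a rule for death matters and are not estimates for this trial.

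The randomised comparison on the primary outcome is untouched.

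**What to change.** - Derive QALYs from the five-dimension EQ-5D index, name the value set, and report the VAS as a descriptive outcome. Make the Quality of Life and Evaluation of Cost of Health Care Services sections name the same source.
- Score utility as 0 from the recorded date of death, and include all randomised patients.
- In the base case, count costs and QALYs over the same week 1–4 window, say so in the cost section, and limit the economic claim to that window.
- If only the VAS was collected, drop the term QALY and present costs beside VAS change.

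The cost section says that patients answer the EQ-5D questionnaire in weeks 1 and 4. If that includes the five dimensions, the index needs no new data and the change is one of wording and analysis. The article does not make certain that the dimensions were collected, so this should be checked first. The downside is a narrower economic claim: a result for weeks 1–4 says nothing direct about the rest of a patient's participation.

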**Methods:**

The telepalliation program will be conducted as a multimethod randomized controlled trial. The intervention group will follow the telepalliation program, while the control group will follow the traditional standard of care program for palliative care. The primary outcome of the study is increased quality of life. Secondary outcomes include enhanced sense of security; reduced experience of pain; satisfactory experiences of patients and relatives with the TelePal platform and degree of satisfaction in being a part of the program; experiences with the use of the TelePal platform on the part of HCPs and the professionals’ experiences of being a part of the program; the use of a cross-sector communication platform and the telepalliation program by patients, relatives, and HCPs; and the projected lower cost of health care services. These outcomes will be assessed using questionnaires, data generated by digital technologies, and semistructured interviews.

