### Data and Network Security

The TelePal platform is web-based. It is possible to access the platform from any internet-enabled device, for example, a PC or Mac computer or a tablet, via any modern browser. The most optimal experience and resolution will appear when using an iPad or tablet. All communication and data are secured based with SSL and a 2-factor log-in. The portal will be kept at AAU on servers provided by AAU IT services.

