### Eligibility Criteria

All participants will be recruited by 2 project nurses at the palliative team at Southwest Jutland Hospital, Esbjerg, Denmark. Recruitment will take place by personal contact and by a recruitment letter. Enrollment will proceed if the participant fits the inclusion and exclusion criteria. Inclusion criteria for participants are that they must be patients under SPC at the Hospital of Southwest Jutland; be aged 18 years or older; live in Esbjerg, Varde, Billund, Fanø, or Vejen municipalities; have cancer, heart failure, chronic obstructive pulmonary disease, or motor neuron disease; and have basic computer skills or have a relative who is able to help them. The exclusion criteria are delirium at enrollment based on the Confusion Assessment Method score; an active psychiatric history other than depression or anxiety related to the main diagnosis, which refers to the reason for palliative care; and a lack of cooperation. Enrollment will take place at the patient’s home, where a doctor and a nurse from the palliative team will take the inclusion and exclusion criteria into consideration. Patients who are moribund are not assessed for participation in the study. The patient will be given complete information about the project, and the palliative team will obtain informed consent. The project nurse will then proceed to explain to the patient how to use the equipment and the TelePal portal. If the patient meets the inclusion criteria and agrees to be included, randomization to either the intervention group or standard care will be made.

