What are the health economy costs of running a telepalliation program? Caraceni et al [11] highlighted the lack of cost-effectiveness studies within telepalliation. In the TelePal study, we will conduct a cost-effectiveness evaluation to show that it will be cost-effective, reduce the cost for transportation, and reduce patients’ travel to the hospitals.

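### The listed cost parameters include no item for operating the TelePal platform, so the planned cost difference leans towards TelePal by an unknown amount

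*Protocol article*

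**What the plan says.** The protocol article, under Evaluation of Cost of Health Care Services, plans a cost-effectiveness analysis by "calculating the differences in clinical efficacy and differences in average cost per patient". It then lists what is costed: "The cost parameters are numbers of phone or video calls from the palliative team, equipment used, driving distance, personal use in palliative care", and "visits from GPs, outpatient clinic visits, numbers of hospitalizations, readmissions, length of stay, and visits from the palliative team". That makes ten items, with no wording that leaves the list open.

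Other sections describe what the program uses. Data and Network Security states: "The portal will be kept at AAU on servers provided by AAU IT services", and mentions a two-factor log-in. The textbox of portal features describes an optional SMS notice. Under Eligibility Criteria the project nurse is to "explain to the patient how to use the equipment and the TelePal portal". Adverse Events and Dropouts says that technical problems are recorded.

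On purpose, the abstract names as a secondary outcome "the projected lower cost of health care services". The Discussion (Principal Findings) asks: "What are the health economy costs of running a telepalliation program", and continues: "we will conduct a cost-effectiveness evaluation to show that it will be cost-effective, reduce the cost for transportation".

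**The concern.** A cost comparison of a digital program with standard care has to set what the program saves against what it takes to run. The list captures where savings could arise: driving, visits, outpatient contacts, admissions and bed days. It has no place for the recurring cost of keeping the platform in operation. If the list is followed as written, that cost is absent from both arms' averages, and the arm that uses the platform for care looks cheaper than it is.

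The secondary outcome of lower cost, and any cost-effectiveness statement, would then rest on an incomplete incremental cost. The Discussion's question about the cost of running the program would remain unanswered.

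**Working it through.** **Step 1. Compare the resources described with the cost list.** The plan gives no cost figure to reproduce, so the check starts by setting the sections side by side.

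| Resource described in the article | Item that could cover it |
|---|---|
| Tablets or other devices | Equipment used |
| Nurse time for set-up and instruction | Possibly the item on personal use, probably meaning personnel |
| Video consultations | Phone or video calls |
| University servers and their maintenance | None |
| Log-in and SMS service | None |
| Technical support | None clearly; hospital staff time might fall under personnel, university IT support would not |

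The gap is therefore platform operation.

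**Step 2. Direction.** Let p_I and p_C be the operating cost per patient in the intervention and control arms. Then

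planned cost difference = true cost difference − (p_I − p_C).

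The planned difference is too low whenever p_I exceeds p_C. The article lets controls complete questionnaires on TelePal or on paper, so p_C need not be zero in the trial. Intervention patients use the portal for messages, video, notes and questionnaires; controls use it at most for questionnaires. So p_I should exceed p_C.

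**Step 3. Size as a formula.** Inputs from the article are 91 patients per arm (Sample Size) and data collection from May 2021 to August 2024, which is 3.25 years, or 40 months if both end months are counted. The annual operating cost F is not given.

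- All of it charged to the intervention arm: 3.25F/91 = 0.0357F, or (40/12)F/91 = 0.0366F per patient.
- If each control carries a fraction c of what an intervention patient carries, then p_I − p_C = (3.25F/91) × (1 − c)/(1 + c). For c = 0.25 this is 0.0357F × 0.60 = 0.0214F. For c = 0.5 it is 0.0357F × 0.333 = 0.0119F. It reaches zero only at c = 1. These values of c are assumptions.
- At a routine volume of n patients a year it is F/n. For an assumed n of 100 to 300, this is 0.0100F to 0.0033F.

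**Step 4. Illustration, with all prices assumed.** Take F = DKK 100,000 to 500,000 a year.

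- Trial volume, 40 months, c = 0: 100,000 × (40/12)/91 = 3,663, and 500,000 × (40/12)/91 = 18,315 DKK per patient.
- Routine volume: from 100,000/300 = 333 to 500,000/100 = 5,000 DKK per patient.
- At an assumed DKK 1,500 to 2,500 per home visit, the full range runs from 333/2,500 = 0.13 of a visit to 18,315/1,500 = 12.2 visits per patient.

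The assumed range runs from negligible to large. It shows how strongly the result depends on F and on volume; it does not estimate the bias.

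**The case against.** The strongest reply is that this is a journal article with a one-sentence cost list. It cites methods sources, and Research Design says that the economic evaluation is done separately at the end; overheads and unit prices are commonly left to a fuller plan. The named outcome is also the cost of health care services, which the ten items fit, and the question about running costs appears only in the Discussion. This has some force for unit prices and allocation rules, whose absence is not criticised here. It does not remove the point. The article enumerates the parameters rather than leaving them open, and they feed a cost-effectiveness comparison in which the intervention's own operating cost belongs.

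Several further objections stand and limit the point:

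- Set-up and training may already be costed, under equipment and personnel. The nurse's instruction on equipment and portal does not settle what the equipment item includes.
- A reader might infer that the platform is treated as free. That goes too far, since equipment and video calls are both listed.
- A reader might infer that the omitted cost falls on one arm only, so that the bias equals the full platform cost. The article does not support this: controls may use TelePal for questionnaires, and Eligibility Criteria describes the portal explanation before randomization.
- No expected cost difference is stated anywhere, so nothing shows that including the platform would reverse the sign of the result.

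**Conclusion.** The point holds for platform operation: hosting, maintenance, log-in and SMS service, and technical support. No listed parameter plausibly covers hosting, maintenance or university IT support, and the article itself shows that the portal depends on university servers. Followed as written, the list makes the difference in average cost per patient too favourable to TelePal.

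The direction rests on one assumption, that an intervention patient carries more operating cost than a control patient, which the described use of the portal supports. The amount cannot be computed from the documents. The documents do not support saying that training is certainly omitted, that the whole platform cost is the bias, or that TelePal would prove more expensive than standard care. This is a cheap improvement to a secondary analysis; the primary outcome is unaffected.

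**What to change.** In Evaluation of Cost of Health Care Services:

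1. Add one parameter: platform operating cost per intervention patient, covering hosting, maintenance, log-in and SMS service, and technical support. Exclude development and research-only use, such as control patients' questionnaires.
2. State that set-up and training time is counted once, either under personnel or under this new line.
3. Report the cost difference at trial volume and at expected routine volume, with the rule for spreading fixed cost over patients.
4. Base any conclusion on cost or cost-effectiveness on the result that includes this parameter.

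The work is a request to the university IT service for running costs, support hours from the project team, and one added line in the analysis. It needs no patient contact and no change to the trial's conduct. The downside is a less favourable incremental cost and an allocation assumption, which reporting at two volumes makes visible.
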